### 4.2. Statistical analysis plan

Baseline variables will be reported using mean and standard deviation, or median and interquartile range for continuous variables, and as counts and percentages for the categorical variables. Correlation analysis will be used for analysing the association between PROMs and continuous variables, including dynamic compensation, spinal imbalance, segmental instability, muscle degeneration and fatigue, and biomechanical parameters. For measuring the association between categorical variables (e.g., the severity of stenosis) and PROMs, we will perform an analysis of variance (ANOVA). Pre- to postoperative differences in PROMs, dynamic compensation, the severity of stenosis, spinal alignment, segmental instability, muscle degeneration, muscle fatigue, and biomechanical parameters will be assessed by comparing means using paired t-tests for continuous variables, and by comparing frequencies using the chi-square test for the categorical variables. Associations of pre- to postoperative changes in PROMs with changes in static and dynamic spinal imbalance, muscle fatigue, and extent of forwarding trunk bending and lumbopelvic range of motion during walking from before to after spinal stenosis operation will be assessed by computing the difference for each variable from before and after surgery for each patient and evaluating the correlation between these computed differences. The statistical methods described here assume the normal distribution of all parameters. In case of

violation of this assumption in the data we will use more appropriate statistical methods (e.g., nonparametric methods). Our predictive model building approach will be based on the seven steps of Steyerberg's [45] to construct a predictive model to predict the surgical outcome from preoperative clinical, functional, radiological, and biomechanical data and musculoskeletal model prediction of postoperative local spinal loads. Data will be checked for accuracy, inconsistencies, and plausibility of the recorded information in the data, and if required re-coding/re-grouping of certain variables will be done. We will restrict categorizing the continuous variables in the model development stage as much as possible to avoid loss of information and assess the predictive ability of the clinically relevant variables (e.g., from preoperative – spinal alignment, segmental instability, muscle degeneration, dynamic compensation, muscle fatigue, and biomechanical parameters) and variables with good/high predictive performance will be used to construct the predictive models. A different set of predictive models will be set up using the candidate predictors with the outcome PROMs. We will compare the predictive performance of the models to select the best-performed model using appropriate statistical methods (e.g., R^2). The predictive models will be based on collected experimental data and also simulated data. As a few of the highly clinically relevant variables cannot be measured directly we will use the experimental data to simulate these variables. For the internal validation of the selected predictive model, we will use cross-validation.

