#### Secondary hypotheses

Hypothesis 2.1: PROMs correlate more strongly with quantitative functional parameters including muscle fatigue, spinal load and biomechanical parameters or lumbopelvic range of motion during forward trunk bending and during walking than with pathomorphological parameters including severity of stenosis, segmental instability and muscle degeneration.

Hypothesis 2.2: Changes in PROMs correlate with changes in static and dynamic spinal imbalance, muscle fatigue and extent of forward trunk bending, lumbopelvic range of motion during walking and spinal loads from before to after spinal stenosis surgery.

Hypothesis 2.3: Patients with sLSS with greater muscle degeneration and greater spinal imbalance have greater muscle fatigue.

Hypothesis 2.4: At follow-up, patients with spinal stenosis will have improved PROMs, less static and dynamic spinal imbalance and muscle fatigue, and less forward trunk bending and larger lumbopelvic range of motion during walking than before spinal stenosis surgery.

Hypothesis 2.5: Postoperative PROMs are explained by preoperative severity of LSS, spinal alignment, segmental instability, muscle degeneration, dynamic compensation, muscle fatigue and spinal load.

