## VII. Radiological parameters

The measurement of *muscle atrophy* and *fatty infiltration* allows quantifying abdominal and paraspinal muscle degeneration. The analysis will be performed using ImageJ image analysis software (Version 1.52t, National Institutes of Health, Bethesda, Maryland) [32, 33].

For L1 to L5, we will measure the *cross-sectional area* (CSA) of the *abdominal and paraspinal muscles* on each side, including the multifidus and the erector spinae (longissimus and iliocostalis) muscles, and the CSA of the vertebral body. The relative CSA (rCSA) will be defined as the ratio between muscle CSA and vertebral body CSA and calculated for each level and side. The CSA of lean muscle in the region of interest will be defined as LeanCSA and measured on each side. The ratio of LeanCSA to the paraspinal muscle CSA will be defined as functional CSA (LeanCSA/CSA), represented as % muscle CSA and calculated for each level and side. Overall

CSA, rCSA and LeanCSA will be computed as average CSA (aCSA), average rCSA (arCSA) and average LeanCSA (aLeanCSA) across all levels considering the muscle as a single unit for each side [34]. In case a different validated (semi-) automated method for assessing muscle degeneration will become available during the study duration, such method will be applied. *Stenosis severity* will be classified according to Schizas [35]. *Segmental instability* will be determined as a relative shift in anteroposterior position of two adjacent segments between the upright standing radiograph and the lying MRI of more than 3mm [36].

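### Hypothesis 2.1 compares correlations, but section 4.2 plans no comparison, and segmental instability is continuous in one section and yes/no in another

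*Protocol*

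**What the plan says.** Protocol, section 2.1, Hypothesis 2.1: "PROMs correlate more strongly with quantitative functional parameters including muscle fatigue, spinal load and biomechanical parameters" (lumbopelvic range of motion is also named on this side) "than with pathomorphological parameters including severity of stenosis, segmental instability and muscle degeneration". This is a statement about a difference between associations.

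Protocol, section 4.2 fixes the methods. PROMs are correlated with "continuous variables, including dynamic compensation, spinal imbalance, segmental instability, muscle degeneration and fatigue, and biomechanical parameters". For graded variables the text reads: "For measuring the association between categorical variables (e.g., the severity of stenosis) and PROMs, we will perform an analysis of variance (ANOVA". The section then covers pre- to postoperative differences, correlations between changes, and a prediction model for surgical outcome. Model performance is compared there (for example by R²), but only to choose the best model for that outcome.

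Protocol, section 3.3, VII: stenosis severity is a classification into grades. Segmental instability is a "relative shift in anteroposterior position of two adjacent segments between the upright standing radiograph and the lying MRI of more than 3mm".

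**The concern.** There are two defects, and both can be read directly from the text.

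First, the hypothesis says one group of associations is stronger than another, but every planned analysis looks at one association at a time. One of the three pathomorphological parameters, stenosis severity, also gets a different kind of statistic from the parameters it is to be compared with. No sentence in section 4.2 sets one association against another.

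Second, segmental instability belongs to the pathomorphological side of the comparison, and its type is contradictory: continuous in section 4.2, a threshold finding in section 3.3. The type decides whether a correlation or a group comparison applies at baseline, and whether a paired t-test or a chi-square test applies to the pre/post change. It also affects how strong its association with PROMs can appear.

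At stake is the answer to the first secondary hypothesis. Without an estimated difference, any statement about which group correlates more strongly would rest on an informal reading of separate results.

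**Working it through.** **Inputs.** From section 4.1: r = 0.3, 80% power, 5% significance, 111 patients (3 × 37), enrolment of 122. The protocol gives no effect size for a difference between correlations, no prevalence of instability, no number of stenosis grades and no correlations between predictors. Values for these are assumptions. Tests are taken as two-sided, because section 4.1 does not say.

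**The plan's own figure.** Section 4.1 sizes the primary correlation, not Hypothesis 2.1. By Fisher's z, detecting r = 0.3 needs 85 patients, or 91 pooled over three strata. The figure of 111 is reproduced exactly as a three-group ANOVA with f = 0.3. Enrolment of 122 follows from 111 × 1.10 = 122.1. Below, 111 serves only as the analysable sample size. At that size a single correlation of 0.3 has power Φ(atanh(0.3) × √108 − 1.96) = Φ(3.217 − 1.96) = 90%.

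**Step 1: matching the hypothesis to the methods.**

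| Parameter in Hypothesis 2.1 | Side | Statistic under 4.2 |
|---|---|---|
| Muscle fatigue, biomechanical parameters | functional | r |
| Muscle degeneration | pathomorphological | r |
| Segmental instability | pathomorphological | r, although defined as yes/no in 3.3 |
| Stenosis severity | pathomorphological | ANOVA F |

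No row leads to an estimate of a difference.

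**Step 2: what ANOVA costs for stenosis severity.** Assume an underlying r of 0.3 cut into 3 or 4 equal grades, n = 111. ANOVA has 73% or 71% power; an ordered (trend) analysis of the same grades has 81% or 84%. On an effect-size scale the distortion runs the other way. With no association, eta is about √((k − 1)/(n − 1)): √(2/110) = 0.13 for 3 grades and √(3/110) = 0.17 for 4. The two scales are therefore not comparable, and neither side is uniformly favoured.

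**Step 3: what the yes/no form of instability would cost.** For a normal shift cut at prevalence p, the observable correlation is r × φ(c)/√(p(1 − p)), with c = Φ⁻¹(1 − p).

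| Assumed prevalence | Factor | 0.30 becomes | Power at n = 111 |
|---|---|---|---|
| uncut | 1 | 0.30 | 90% |
| 10% | 0.585 | 0.18 | 45% |
| 20% | 0.700 | 0.21 | 60% |
| 30% | 0.759 | 0.23 | 67% |

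**Step 4: why significant versus non-significant is no substitute.** Let both true associations be 0.3, with the two tests treated as independent. The functional variable is significant and the other is not with probability:
- both continuous: 0.896 × 0.104 = 9%
- second variable yes/no at 20% prevalence: 0.896 × 0.399 = 36%, against 0.601 × 0.104 = 6% for the reverse.

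All these discordances arise with no difference between the underlying associations.

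**Step 5: what a proper comparison could show.** For two correlations sharing the same PROM, the standard error of the difference in Fisher z is √((2 − 2c₁₂)/(n − 3)), where c₁₂ is the Dunn–Clark/Steiger covariance term. For 0.3 against 0.1 the difference is 0.3095 − 0.1003 = 0.2092. Results for a correlation between the two predictors of 0 / 0.3 / 0.5:

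| True correlations | Power at n = 111 | n for 80% power |
|---|---|---|
| 0.3 vs 0 | 62% / 78% / 90% | 167 / 118 / 85 |
| 0.3 vs 0.1 | 33% / 44% / 58% | 368 / 260 / 187 |
| 0.3 vs 0.2 | 12% / 15% / 19% | 1421 / 1006 / 724 |

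**The case against.** **A separate analysis plan may supply the test.** It may, and silence alone would not be a finding. But section 4.2 already assigns a method to each type of variable, and those methods give no common measure. The conflict between sections 3.3 and 4.2 also lies within the protocol itself.

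**Section 4.2 may simply mean the shift in mm.** This is a fair reading, helped by its stated wish, for model development, to limit categorising of continuous variables. If so, the loss in Step 3 does not arise and section 3.3 is what needs aligning. The loss is therefore conditional; the contradiction is not.

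**ANOVA is a small matter.** Largely true. It touches stenosis severity only, the power loss is modest, and eta is biased upward. What stands is that F and r cannot be ranked against each other.

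**Stronger readings that the protocol does not support.** A reader might infer that the functional set is much larger, so that its largest correlation wins by chance. The protocol gives no such counts. Section 3.3 derives muscle measures at five levels on two sides: for one muscle group, relative and functional cross-sectional area alone give 2 × 5 × 2 = 20 values. Even the three side averages give 3 × 2 = 6, or 8 with severity and instability. A reader might also infer that scale, cut-point and number of variables all tilt the plan towards its hypothesis. Steps 2 and 3 and these counts do not establish that. Nor does the protocol say that Hypothesis 2.1 will be judged by counting significant results; Step 4 shows only why that would be unsound.

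**Conclusion.** The point holds in two parts that need no assumptions. Section 4.2, followed as written, yields no estimate of the difference that Hypothesis 2.1 asserts, and it puts one pathomorphological parameter on another scale. Sections 3.3 and 4.2 also disagree on whether segmental instability is continuous or yes/no, and must be reconciled.

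The size of the second part is conditional. If the yes/no form is analysed, an underlying 0.30 appears as 0.18–0.23, with power of 45–67% instead of 90%. This assumes a normal shift, prevalences of 10–30% and n = 111. If the shift in mm is analysed, there is no loss.

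The hypothesis is secondary and the primary correlation is unaffected. The text should be changed before analysis, but the design need not be.

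**What to change.** 1. In the association analyses, use the measured shift in mm (stating which level, for example the largest) and keep the 3 mm cut as descriptive. Align sections 3.3 and 4.2.
2. Treat stenosis grade as an ordered score and use Spearman correlation for every variable in the comparison, so that all associations are on one scale.
3. List in advance the functional and pathomorphological variables to be compared, and name ODI as the PROM. Estimate either the difference in absolute correlation for prespecified pairs (Steiger or Meng; bootstrap if Spearman is used), or the difference in cross-validated R² between the two listed blocks, with a 95% confidence interval. Conclude that one side correlates more strongly only if the interval excludes 0.
4. State that precision is modest and that Hypothesis 2.1 will be reported mainly as an estimate with its interval.

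The cost is wording and programming, since the shift must already be measured to apply the cut. There are two drawbacks. At n = 111, an interval excluding 0 is likely only for large differences (Step 5). The block version answers a question about joint rather than individual association, so the choice between the two versions must be made beforehand.

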### **3. PROJECT POPULATION AND STUDY PROCEDURES**

#### **3.1 Project population, inclusion and exclusion criteria**

We plan to include 122 patients with sLSS (61 per year) in this study, which will be realistic and sufficient for the proposed statistical analysis (see Section 4.1). Patients will be recruited at the Department of Spine Surgery at the University Hospital Basel. The surgical procedure is not affected by the study and is not subject of investigation. All patients will receive – depending on their clinical and imaging diagnostics – lumbar decompression alone or decompression combined with fusion either through posterolateral fusion with pedicle screw-rod system with autologous bone apposition or through transforaminal lumbar interbody fusion with a cage filled with autologous bone implanted from posterolateral into the intervertebral space. Decompression will be performed as either open surgery or microsurgical technique, and both are performed through a midline approach. The open surgery decompression will be performed via an interspinous approach with interlaminar flavectomy, whereas in the microsurgical technique, uni- or bilateral fenestration and flavectomy will be performed.

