#### **XVI. Surgical information**

Information on the surgical procedure will be extracted from the patient files:

11. Scheduled decompression surgery
12. Scheduled fusion of vertebrae
13. Number of decompressed levels
14. Number of instrumented levels
15. In case of instrumentation:
  - Fusion with Cage
  - Fusion without Cage

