### **6 FURTHER ASPECTS**

#### **6.1 Overall ethical considerations**

Study participation is voluntary. Assessing the proposed study parameters in addition to standard clinical measures will provide additional insight into the functional limitations and the clinical course of the stenosis in our patients. This study represents a considerable time effort by the participants. However, results of the study assessments will be considered in the ongoing treatment planning and this time effort may be outweighed by the benefits not only for future patients but also for the study participants.

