#### **6.2 Risk-Benefit Assessment**

This project is a risk category A project. Collecting health-related personal data in this study entails minimal risks and burdens for the patient. Double sided tape will be used to attach inertial sensors and skin markers on specific anatomic landmarks. The tape may cause some skin irritation similar to a standard band-aid. Participants may experience some skin irritation at the location of skin electrodes because these locations have to be shaved and cleaned prior to electrode application. The modified Biering-Sørensen test is comparable to situations during daily, occupational or recreational activities. Overground gait analysis bears minimal risks for the patient. The MRI risk of the spine can be neglected. This standardized examination is performed in daily clinical practice. No contrast media will be given. Patients with pacemakers, neurostimulators or other incompatible devices will be excluded. All female patients prior to menopause will complete a pregnancy test before the MRI scan. If the test is positive, the patient will be excluded. EOS radiological imaging is routinely used in clinical practice. This measurement involves a minimal radiation risk (see 5.4). Measurement with Artec EVA is radiation free and fast and can lead to important conclusions about the status of the external shape and postures of patients with sLSS. This study provides no direct benefit to the patient or healthy participant. Participants will be compensated with 100 CHF for each visit. Treatment of patients with sLSS is not part of the study and will not be influenced by study participation.

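### Section 4.2 names no procedure term for the change correlations (H2.2) or the pre/post comparisons (H2.4), although the cohort mixes decompression alone with fusion and the procedure is recorded

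*Protocol*

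**What the plan says.** Protocol section 3.1 says that patients receive "lumbar decompression alone or decompression combined with fusion", the choice "depending on their clinical and imaging diagnostics". It adds that the operation is not itself under investigation. Neither the expected split nor the size of any procedure difference is given.

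The operation is documented. Section 2.2 (Other parameters, XVI) lists scheduled fusion, cage use and the numbers of decompressed and instrumented levels. Section 3.3 (XVI) says "Information on the surgical procedure will be extracted from the patient files".

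Hypothesis 2.2 relates changes in PROMs to changes in imbalance, fatigue, trunk bending, lumbopelvic motion and spinal loads. Hypothesis 2.4 expects, among other improvements, "larger lumbopelvic range of motion during walking than before spinal stenosis surgery". Hypothesis 2.5 explains postoperative PROMs from preoperative findings. None of the three mentions the procedure.

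Section 4.2 compares "Pre- to postoperative differences in PROMs, dynamic compensation, the severity of stenosis, spinal alignment, segmental instability, muscle degeneration, muscle fatigue, and biomechanical parameters" with paired t-tests (chi-square tests for categorical variables). For H2.2 it forms a before/after difference per patient and correlates the differences. No procedure term or stratum appears in either analysis.

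On a related matter, section 6.1 says that "results of the study assessments will be considered in the ongoing treatment planning", while section 6.2 says "Treatment of patients with sLSS is not part of the study and will not be influenced by study participation". Sections 3.1 and 3.2 agree with 6.2.

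**The concern.** Fusion with a screw-rod system or a cage fixes segments, so it can directly alter several variables whose changes are studied: alignment, lumbopelvic range of motion and spinal load. This is subject-matter reasoning; the protocol does not quantify it. If the procedures also differ in PROM change, procedure is a common cause of both sides of the H2.2 correlation. A correlation could then appear with no relation between biomechanics and symptoms among patients who had the same operation. If the two shifts run in opposing directions, a real relation could be masked.

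For H2.4 the matter is interpretation. The pooled mean change averages over two operations in whatever proportion the clinic happens to perform them. The expectation of larger lumbopelvic motion is also less obvious where segments have been fixed. Section 1 wants the results to inform targeted therapy, so readers will want to know which patients a change describes.

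**Working it through.** **Inputs from the protocol.** Section 4.1 gives a target correlation of 0.3, 80% power, 5% level, 111 patients required, 10% drop-out and 122 enrolled. Completers: 122 × 0.9 = 109.8, about 110. Sidedness is not stated; two-sided is assumed below.

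**The plan's own figure.** Fisher's z for a simple correlation of 0.3 needs 85 patients, not 111. The figure 111 is reproduced by a three-group F test (2 df) with Cohen's f = 0.3, power 0.803. It concerns the primary hypothesis and is not in dispute here.

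**Spurious correlation from pooling.** Assumptions, none from the documents: fusion share p of 20% to 50%, zero correlation within each procedure, equal within-procedure SDs, and procedures differing by d SD on both change scores. With q = p(1 − p), the pooled correlation is r = q·d² / (1 + q·d²). At p = 0.2, q = 0.16; at p = 0.5, q = 0.25.

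- d = 0.3: 0.0144/1.0144 = 0.014 to 0.0225/1.0225 = 0.022
- d = 0.5: 0.04/1.04 = 0.038 to 0.0625/1.0625 = 0.059
- d = 0.8: 0.1024/1.1024 = 0.093 to 0.16/1.16 = 0.138
- d = 1.0: 0.16/1.16 = 0.138 to 0.25/1.25 = 0.200

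The chance of a significant result at N = 110 is Φ(atanh(r)·√107 − 1.96) + Φ(−atanh(r)·√107 − 1.96). Against the nominal 5% this gives 5–6%, 7–9%, 16–30% and 30–56% for the four values of d.

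If the shifts differ, d₁ on the biomechanical change and d₂ on the PROM change, r = q·d₁·d₂ / √((1 + q·d₁²)(1 + q·d₂²)). At an assumed p = 0.4 (q = 0.24):

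- (d₁, d₂) = (1, 0.3): r = 0.064
- (1, 0.5): r = 0.105
- (1.5, 0.5): r = 0.141

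**Mean change.** The pooled mean is (1 − p)·m_D + p·m_F, where m_D and m_F are the mean changes after decompression alone and after fusion. The paired test is valid for this quantity, but its value moves with p.

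**Cost of adjusting.** Power for r = 0.3 at N = 110, with atanh(0.3) = 0.3095:

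- unadjusted: Φ(0.3095·√107 − 1.96) = 0.893
- one binary covariate: Φ(0.3095·√106 − 1.96) = 0.890

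The required n rises from 85 to 86.

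**Cost of splitting instead.** At a fusion share of 20% to 50% (22 to 55 patients), power for r = 0.3 within the fusion group is 27% to 61%. In the decompression-alone group (88 down to 55 patients) it falls from 81% to 61%. Adjustment is therefore preferable to separate correlations.

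**The case against.** Several counter-arguments have force.

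- **The protocol never says that procedure will be ignored.** A further analysis plan, not shown, could add adjustment. That stands. But section 4.2 does fix the tests for these hypotheses, and the adjusted version is better at almost no cost.
- **The three-level covariate in section 4.1 might cover it.** That covariate is unnamed, is tied to the primary correlation, and is not taken up in 4.2.
- **Surgery is not under investigation, and H2.4 asks only whether patients change.** The whole-cohort mean answers that question. A reader might infer that the pooled paired test is wrong; it is not. Only its interpretation is limited. One can choose a fusion share and opposite changes that cancel exactly (0.6 × 0.4 − 0.4 × 0.6 = 0, in SD), but nothing in the protocol indicates such shifts.
- **Prediction.** A reader might infer that the prediction models leave procedure out. Section 4.2 introduces its predictors as examples and neither names nor excludes it, and scheduled fusion is known before surgery. A model predicting outcome under routine care may validly omit the operation, so forcing it in would be a preference.
- **Segmental instability.** It is tempting to cite this as the clearest case, since fusion acts on it directly. It is in the 4.2 pre/post list and in H2.1 and H2.5, but not in H2.2 or H2.4.
- **Treatment planning.** A reader might infer from section 6.1 that the studied predictors steer the choice of operation. Patients enter already scheduled for surgery (section 3.1), and 6.1 does not mention the choice of procedure. The conflict with 6.2 is real; that consequence is conjecture.

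**Conclusion.** The point holds as a cheap improvement to the secondary analyses. Section 4.2 correlates change scores across a surgically mixed cohort without the recorded procedure, so the H2.2 correlations can partly reflect which operation was done. The H2.4 mean change is valid but depends on case mix.

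The size cannot be known from the documents. Under the stated assumptions the distortion is small (r about 0.01–0.06) when procedures differ by 0.3–0.5 SD on both changes. It becomes material against a target of 0.3 only at about 0.8 SD or more on both (r 0.09–0.20). The protocol supports no particular value.

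H1 and the sample size are not affected. The contradiction between section 6.1 and sections 3.1, 3.2 and 6.2 is a separate matter of wording.

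**What to change.** In section 4.2:

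- **H2.2:** estimate the change correlations as partial correlations, or the equivalent regressions, adjusted for fusion (yes/no).
- **H2.4:** keep the pooled test and report changes descriptively for decompression alone and for decompression with fusion, with confidence intervals.
- **H2.5:** name scheduled fusion among the candidate predictors.

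The cost is a few lines of text and one model term (power 0.893 to 0.890). The variable is already collected. Intervals in the smaller procedure group will be wide, which is why the by-procedure results should be descriptive.

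Separately, reconcile section 6.1 with sections 3.1, 3.2 and 6.2 on whether study results reach treatment planning.

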## 2.3 Project design

This study is designed as a single-center, longitudinal observational study. For each patient, a multimodal set of data including experimental, clinical, functional, radiological and biomechanical data is compiled before and after routine surgical intervention. There will be two study visits: baseline and one-year follow-up (Figure 1).

[figure not shown]

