## 4 STATISTICS AND METHODOLOGY

### 4.1 Sample size calculation

To determine if PROMs correlate with dynamic compensation considering categorical covariates with 3 levels of the covariate a sample size of 111 (37 within each level) is required to detect a correlation of 0.3 at 80% power and 5% significance level. Considering a 10% drop-out rate, 122 subjects will be enrolled in the study.

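### The planned chi-square comparison of pre- and postoperative categories ignores that both measurements come from the same patient (should be fixed; secondary comparisons only)

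*Protocol*

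**What the plan says.** Section 2.3 describes a longitudinal study in which each patient's data set "is compiled before and after routine surgical intervention", and adds: "There will be two study visits: baseline and one-year follow-up".

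Section 4.2 lists the variables whose pre- to postoperative difference will be assessed. Severity of stenosis and segmental instability are among them. The methods are "comparing means using paired t-tests for continuous variables", "and by comparing frequencies using the chi-square test for the categorical variables". Pairing is named for means and not for frequencies.

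Section 3.3, item VII, says what kind of variables these are. Stenosis severity is a Schizas classification, and Section 4.2 itself gives severity as its example of a categorical variable. Segmental instability is a relative shift of adjacent segments "between the upright standing radiograph and the lying MRI of more than 3mm", which is a yes/no criterion. Yet the correlation sentence of Section 4.2 lists segmental instability among the continuous variables.

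Section 4.2 also allows a change to other methods, such as nonparametric ones, but only if normality is violated.

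**The concern.** A chi-square comparison of the pre and post frequencies takes the 111 baseline and 111 follow-up values as 222 independent observations. They are 111 pairs. The test's variance omits the within-patient covariance, so its error rate is not the nominal 5% unless that covariance is zero. For the stenosis grade the test also ignores the order of the categories.

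At stake is whether the reported p-values for categorical change mean what they say. They would stand beside paired t-tests that do respect the design. With positive within-patient correlation a real change of moderate size can be missed; with negative correlation the test rejects too often.

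**Working it through.** **Inputs.** The protocol gives no rate, correlation or power for this comparison, so there is no figure of its own to reproduce. The number of pairs is taken from Section 4.1: "a sample size of 111 (37 within each level) is required". Tests are two-sided at 5%. Rates at each visit (p1, p2) and the within-patient correlation phi are assumptions, shown over a range.

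**1. Size of the test, binary variable, no change (p1 = p2 = p).** The true variance of the difference in proportions is 2p(1-p)(1-phi)/n. The chi-square test uses 2p(1-p)/n. Its z statistic therefore has variance 1-phi, and the true size is P(|Z| > 1.96/sqrt(1-phi)).

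| phi | 1.96/sqrt(1-phi) | Size, formula | Chi-square, simulated at 30%/30%, n = 111 | McNemar, simulated |
|---|---|---|---|---|
| -0.2 | 1.789 | 7.4% | 7.1% | 4.8% |
| 0 | 1.960 | 5.0% | 5.0% | 4.9% |
| 0.3 | 2.343 | 1.9% | 2.0% | 5.2% |
| 0.5 | 2.772 | 0.6% | 0.6% | 5.4% |

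(40,000 runs per setting.)

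**2. Power, binary variable, 30% to 20%, n = 111.** The chi-square test rejects when the difference exceeds 1.96 x sqrt(2 x 0.25 x 0.75/111) = 0.114. The true variance per pair is 0.21 + 0.16 - 2 phi x sqrt(0.21 x 0.16) = 0.37 - 0.367 phi. At phi 0.5 this is 0.187, the standard error is sqrt(0.187/111) = 0.041, and power is the normal probability below (0.100 - 0.114)/0.041 = -0.34, that is 37%. Simulated powers:

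| phi | Chi-square | McNemar |
|---|---|---|
| 0 | 40% | 40% |
| 0.3 | 39% | 55% |
| 0.5 | 37% | 70% |

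For 40% to 25% the pairs are 67/66%, 70/82% and 73/94%. For large changes (80% to 50%, 80% to 30%, 40% to 10%) both tests exceed 99% at every feasible phi tried, and they differ by less than 1 point.

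**3. Ordered grade.** The protocol does not state the number of grades. Assume four grades of equal size, a shift of 0.3 latent SD and n = 111 (3,000 runs). Chi-square against Wilcoxon signed-rank gives 38/52% at latent correlation 0, 35/65% at 0.3 and 31/83% at 0.6. The gap at correlation 0 comes from ignoring the order; its widening comes from ignoring the pairing. At a shift of 0.8 SD both tests have power of about 99.8% or more.

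**4. One data set, two answers.** Take 33/111 positive before and 22/111 after, with 14 patients changing from positive to negative and 3 the other way (phi 0.62).
- Chi-square: z = (11/111)/sqrt(2 x 0.248 x 0.752/111) = 1.71, p = 0.087.
- McNemar: (14-3)²/(14+3) = 7.12, p = 0.008 (exact 0.013).

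**5. The other way to run a chi-square.** Applied to the pre-by-post cross-table, it tests association and not change. With 30% at both visits, so no change at all, it rejects in 87% of runs at phi 0.3 and 99.9% at phi 0.5.

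**The case against.** **The wording may cover McNemar.** McNemar's statistic is also referred to a chi-square distribution, and the text does not say Pearson. But the sentence attaches pairing only to the t-test and speaks of comparing frequencies, whereas McNemar's test compares discordant pairs. The unpaired reading is the natural one. The fallback does not rescue it, because it is triggered by non-normality and not by pairing.

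**The error is mostly conservative.** This stands for positive correlation, which is the more plausible case: the size falls below 5% and there are no extra false claims. The p-values are still not what they purport to be, and under negative correlation they are too small.

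**The loss of power is conditional.** This stands. A reader might infer that the chosen test must lose much power. The documents do not support that: they give no rates, shift or within-patient correlation. All patients undergo decompression, so a large change in stenosis grade, with negligible loss, is quite possible.

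**Segmental instability may not be affected.** This stands as an ambiguity. If it is analysed as continuous, as the correlation sentence implies, it gets the paired t-test. Stenosis severity remains affected either way.

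**No hypothesis depends on the test.** This also stands. A reader might infer that the main conclusions are at risk. Hypothesis 2.4, on change after surgery, lists PROMs, spinal imbalance, muscle fatigue, forward bending and lumbopelvic motion; it names neither stenosis severity nor instability. The primary endpoints are the ODI and dynamic compensation.

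**Conclusion.** The point holds in limited form. As written, Section 4.2 applies an unpaired test to paired categories, and its true error rate departs from 5% whenever the two measurements are correlated. That follows from the design and does not depend on the assumed effect; how far it departs depends on phi.

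The cost in power, by contrast, rests on assumption. For a binary variable and the moderate changes tried (10 to 15 points), it runs from nothing at phi 0 to about 20 to 33 points at phi 0.5, and it is under 1 point for changes of 30 points or more. For the ordered grade there is a further loss from ignoring order when the shift is small.

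Only secondary pre/post comparisons are concerned. This should be fixed before analysis, but it does not threaten the study's primary result.

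**What to change.** In Section 4.2, replace the chi-square clause with, for example: Paired binary variables will be compared between baseline and one year with McNemar's test (exact version), and the stenosis grade with a paired ordinal test (Wilcoxon signed-rank); the pre/post cross-table will be shown for each.

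For the grade, a marginal-homogeneity test (Stuart-Maxwell) or a cumulative-logit model with a patient random effect would also respect the pairing. What matters is that one is named in advance.

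Add a sentence stating whether segmental instability is analysed as the yes/no criterion or as a continuous shift, and make the correlation sentence agree with it.

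The cost is two sentences. No new data, visits or patients are needed, and the sample size does not change. Making the change before the follow-up data are analysed avoids a later switch of test made with the results in view.
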